#### Data Analysis for Primary Aim

For each of the 3 primary response variables, the immediate changes in the pre to post treatment measurements at BL2 and the changes in the pre-treatment variables from BL2 to week 2 will be compared across the 3 treatment groups using analysis of covariance (ANCOVA) adjusting for the minimization variables. The following 2 preplanned contrasts for the 2 degrees of freedom for treatment will be tested at 0.05: HVLA-SM vs. sham control and LVVA-SM vs. sham control on the adjusted means based on the ANCOVA model. Residual plots will be used to assess the adequacy of the model assumptions. Data transformations will be explored when model assumptions are violated. Further adjustments for the following baseline characteristics will be explored to increase the precision of the estimated effects: RMDQ, NRS, Quebec Task Force classification, Beck Depression Inventory and chiropractic care (yes/no). Adjusted group means and mean differences between SM and control groups will be reported with 95% confidence intervals determined under the final ANCOVA model.

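### The primary tests and the reported confidence intervals are not tied to one prespecified ANCOVA model

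*Protocol article*

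**What the plan says.** All of this stands in one paragraph of the protocol article, Data Analysis for Primary Aim, in this order:

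- Changes in the three sway variables, pre to post treatment at BL2 and pre-treatment BL2 to week 2, are analysed "using analysis of covariance (ANCOVA) adjusting for the minimization variables". No other model has been named up to that point.
- On testing, the text reads: "The following 2 preplanned contrasts for the 2 degrees of freedom for treatment will be tested at 0.05". Each sets one manipulation arm against sham, and the model it rests on is called simply the ANCOVA model.
- Model fit is then judged from residual plots, with an open remedy: "Data transformations will be explored when model assumptions are violated".
- Covariate choice comes next: "Further adjustments for the following baseline characteristics will be explored to increase the precision of the estimated effects". Five are named: the disability score, the pain rating, Quebec Task Force class, the depression score, and chiropractic care as yes or no.
- Last comes the source of what will be published. The adjusted means, their differences and the 95% intervals are those "determined under the final ANCOVA model".

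The article does not say whether the model behind the 0.05 tests is the starting one or the final one. Data Analysis for Secondary Aim a applies the same approach to the remaining sensorimotor variables and reports only means, differences and intervals. Those are the quantities tied to the final model.

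**The concern.** The paragraph describes a procedure: start from one model, explore, then report from the model arrived at. Residual plots and the precision of an estimated effect can be judged only with outcome data, so the reported estimate and interval are conditional on a choice made from those data.

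Two things are at stake. First, the test and the interval for the same primary contrast can disagree, and the reader has no rule for which one carries the conclusion. Second, a transformation could move the estimate off the scale on which the trial was planned. The footnote to Table 3 gives effects of 4 mm/sec, 1 mm and 0.5 mm, and different sway measures could end up on different scales or with different covariates.

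**Working it through.** **The plan's own figures.** Sample size justification inflates 63 per group by 15%: 63 × 1.15 = 72.45, so 73, and 3 × 73 = 219, as stated. Table 3 rests on one-way ANOVA without covariates. For a 1-df contrast, power comes from the noncentral F with λ = n·d²/2 on (1, 3n − 3) df. Foam sway speed at 86% with n = 73 implies d = 0.505. With n = 63 that predicts 80.6%, against 80% stated. All nine numeric Power B entries reproduce within 1 point in this way. The published design figures therefore do not depend on which ANCOVA is finally chosen.

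**Two readings of the paragraph.**

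- *Tests on the starting model, intervals on the final model.* The tests stay prespecified as to covariates, but P-value and interval may conflict.
- *Tests and intervals both on the final model.* They agree, but both follow selection.

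**How many models.** Five optional covariates give 2⁵ = 32 subsets, before any transformation. Table 2 collects the pain rating at both BL1 and BL2, and the paragraph does not say which is meant. The choice could be made separately for 3 variables × 2 endpoints = 6 analyses, or 12 if solid and foam surfaces are analysed apart, as Table 3 shows them.

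**Type I error by selection rule.** Null simulation with three equal arms, simplified minimization terms in every model and five candidate covariates. Two of the candidates together explain 0% or 10% of outcome variance (an assumption). All 32 subsets were fitted, with 5,000 runs per row and one contrast against sham, two-sided 0.05. Monte Carlo standard error is √(0.05 × 0.95 / 5,000) ≈ 0.3 points.

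| n per arm | variance explained | minimization terms only | all five fixed | AIC | smallest SE | smallest P |
|---|---|---|---|---|---|---|
| 63 | 0% | 5.0% | 5.0% | 5.2% | 5.2% | 6.8% |
| 63 | 10% | 4.7% | 5.0% | 5.2% | 5.3% | 8.8% |
| 73 | 0% | 5.4% | 5.7% | 5.6% | 5.4% | 7.2% |
| 73 | 10% | 5.1% | 5.7% | 5.6% | 5.6% | 9.0% |

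Within a row, selecting on AIC or the smallest standard error adds at most about half a point to the minimization-only model (5.26 − 4.74 = 0.52). Selecting on the P-value adds up to about 4 points (8.82 − 4.74 = 4.08).

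A second set of 6,000 runs used skewed data and a raw-or-log choice:

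- scale chosen by a residual normality test: 5.1–5.6%
- the same, plus smallest-SE covariates: 5.7–5.8%
- scale chosen by smallest P: 6.9–7.2%
- smallest P over 32 subsets × 2 scales: 10.1–10.9%

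**Discordance under the first reading.** At n = 63 with 10% of variance explained, the mean standard error is 0.1791 for the minimization-only model and 0.1705 for the smallest-SE model, a ratio of 0.952. The critical t on 189 − 6 = 183 df is about 1.97. With the estimate held fixed, a starting-model t between 1.97 × 0.952 ≈ 1.88 and 1.97 would be non-significant while the reported interval excludes zero. In practice the estimate shifts too, so a conflict can run either way.

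**The case against.** The strongest reply is that the plan does specify a primary analysis. It names an ANCOVA with three minimization factors and two preplanned contrasts before any exploration is mentioned, and attaches the final model only to estimates and intervals. The covariates are a closed list of baseline variables, the stated purpose is precision, and transformation is conditional on violated assumptions. Selection rules usually sit in an SAP, and this is a condensed article from a developmental grant.

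Most of that stands, and it rules out several stronger readings that a reader might infer:

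- *That no primary model exists, or that the primary P-values are not those of a prespecified test.* This is not established: the contrasts are tied to an ANCOVA introduced with the minimization variables only, and the text is ambiguous about what happens next.
- *That type I error reaches 17%.* A simulation can give 16.7%, but only if the smallest treatment P-value is picked and each of five covariates explains 8% of variance (5 × 8% = 40% if independent). The text plans no such selection, and nothing in it supports covariates that strong for sway changes.
- *That model checking is done unblinded, or that change scores will be logged.* The article says neither; a transformation could be applied to raw sway values before differencing.

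The appeal to an unseen SAP does not dispose of the point. The missing selection rule could be left there, but the article itself assigns the reported intervals to a model reached by exploration. An SAP that fixed one model would change that stated method.

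**Conclusion.** The point holds in limited form. Reported primary estimates and 95% intervals come from a model settled after exploring transformations and covariates on outcome data, and the article leaves open whether the 0.05 tests use that model. P-value and interval may therefore come from different models, or both may be post-selection.

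If the stated aims govern the choice, the effect is small: about 5–6% per contrast in place of 5%. The 7–11% range needs selection on the treatment contrast. These figures rest on the simulated covariate strength (0–10% of variance), simplified minimization terms and, for the transformation runs, skewed data; the documents give no figures for any of these. One further effect cannot be sized: missing data are not imputed, so a covariate with missing values would also change who is analysed. The remedy is nearly free, so the change is worth making despite the modest size.

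**What to change.** Name one model that supplies both the 0.05 tests and the reported estimates and intervals, identical for all primary variables and both endpoints. It should contain:

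- arm;
- the three minimization factors;
- the pre-treatment BL2 value of the outcome, which Table 2 shows is already collected;
- any of the five listed covariates the investigators want, chosen before outcome data are seen by arm, with the visit stated for the pain rating.

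Settle any transformation, for example of raw sway values, in advance or on blinded pooled data. Report every other adjustment or transformation as a sensitivity analysis, and carry the same rule into the secondary sensorimotor variables.

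The cost is wording, plus a small possible loss of precision if an omitted covariate proves prognostic. In the simulation at n = 63, fixing all five covariates cut the mean standard error from 0.1791 to 0.1735 (about 3%) when they explained 10% of variance, and raised it from 0.1793 to 0.1829 (about 2%) when they explained none. The baseline sway value should help: with equal pre and post variances and correlation ρ, it multiplies the standard error of an unadjusted change-score comparison by about √((1 + ρ)/2), which is never above 1. No stated sample size, alpha or power figure changes.

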#### Data Analysis for Secondary Aim a

The remainder of the sensorimotor variables will be analyzed as above. However, only group means and mean differences between SM and control groups with 95% confidence intervals will be reported, not P-values.

#### Data Analysis for Secondary Aim b

There is no control group at 6 weeks. Therefore, changes between pre-sensorimotor variables collected at BL2 and week 6 for those allocated to the SM groups will be described separately for HVLA-SM and LVVA-SM. Means and mean differences with 95% confidence intervals will be reported for each variable.

#### Data Analysis for Secondary Aim c

Clinical outcome assessments considered include the NRS, the RMDQ and SF-36 subscales, physical function and bodily pain. Correlation coefficients and 95% confidence intervals will be reported for changes in sensorimotor response variables against changes in the outcome assessments at BL2, week 2 and week 6 time points overall and by treatment group.

## List of abbreviations

AE: adverse events; ANCOVA: analysis of covariance; AZ: Arizona; BDI-II: Beck Depression Inventory version II; BL1: baseline visit 1; BL2: baseline visit 2; CA: California; CATI: computer assisted telephone interview; cm: centimeter; CONSORT: Consolidated Standards of Reporting Trials; CR: case review; EAC: External Advisory Committee; e.g.: *exemplie gratia *or for example; DSMC: Data and Safety Monitoring Committee; EMG: Electromyography; FDA: Food and Drug Administration; HA1: Health Assessment 1; HA2: Health Assessment 2; HIPAA: Health Insurance Portability and Accountability Act; HVLA-SM: high-velocity low amplitude spinal manipulation; Hz: Hertz; IA: Iowa; i.e.: *id est *or that is; ID: identification; IL: Illinois; Int: Interview; IRB: Institutional Review Board; kg: kilogram; L3: third lumbar vertebra; LBP: low back pain; LVVA-SM: low-velocity variable-amplitude spinal manipulation; MA: Massachusetts; MN: Minnesota; MS: Microsoft; N: Newton; NC: North Carolina; NCCAM: National Center for Complementary and Alternative Medicine; NIH: National Institutes of Health; NRS: Numerical pain rating scale; OH: Ohio; PCC: Palmer college of Chiropractic; PCCR: Palmer Center for Chiropractic Research; PS: Phone Screen; QCA: Quad Cities Area; QTF: Quebec Task Force RMDQ: Roland-Morris Disability Questionnaire; S1: first sacral segment; SAE: serious adverse events; SF-36: Medical Outcomes Study 36-Item Short-Form Health Survey; SM: spinal manipulation; SQL: Structured Query Language; T1: first thoracic vertebra; VT: Vermont.
